# SUMMARY

Following the rapid development of significant drug resistance of *Plasmodium falciparum* (Pf) to chloroquine and then sulfadoxine-pyrimethamine (the first line therapy in Ethiopia 1998-2004), artemether- lumefantrine (Coartem or AL) was adopted as first line therapy in Ethiopia in 2004. According to the current national malaria diagnosis and treatment guidelines, first-line treatment for uncomplicated falciparum infection is AL. First-line treatment for *Plasmodium vivax* (Pv) is with chloroquine (CQ) alone without primaquine therapy in malarious areas. For all clinical infection without laboratory confirmation, AL which is effective against both Pf and Pv is the first-line treatment. Thus, in Ethiopia, where treatment for malaria without laboratory confirmation occurs frequently, Pv is often treated with AL as the standard of care. Furthermore, World Health Organization (WHO) recommends AL for the treatment of Pv, where AL has been adopted as first-line treatment for Pf. Now with wide-spread use of AL and CQ, we propose to conduct an antimalarial efficacy study to monitor the effectiveness of these therapies in Ethiopia and to determine how efficacious these drugs remain. This information will inform future policy changes with respect to appropriate antimalarial strategies.

The simplest and most universally accepted measure of testing for antimalarial drug treatment efficacy, the standardized procedures outlined in the World Health Organization *Assessment and monitoring of antimalarial drug efficacy for the treatment of uncomplicated falciparum malaria* and the WHO *Monitoring antimalarial drug resistance*, will be followed.

In this proposal, patients aged above 6 months with symptomatic malaria presenting to health centers will be enrolled for treatment with AL for *P. falciparum* infection, and either AL or CQ for *P. vivax* infection. Clinical, parasitologic, and hematologic parameters will be monitored for *P. falciparum* and *P. vivax* infection over a 42-day follow-up period, which will be used to evaluate drug efficacy. Results from this research study will be used to assist Ethiopia in assessing their current national malaria drug policies.

# INTRODUCTION

The impact of malaria on the health and economic development of human populations is greatest in the tropics and sub-tropics [1]. The World Health Organization (WHO) has estimated 247 million cases of malaria and 881 000 deaths occurred in 2006 making it one of the world's leading killers [2]. Children under 5 years of age living in sub-Saharan Africa account for the majority of the illness and death caused by malaria worldwide. There are substantially less data on individuals 5 years of age and above.

Most countries in sub-Saharan Africa have adopted the WHO Global Strategy for Malaria Control, which relies primarily on prompt and effective antimalarial treatment. The ultimate success of this strategy rests on the ability of governments to provide antimalarial drugs which are indeed efficacious. Because of wide-spread and intensifying antimalarial drug resistance to a variety of currently available antimalarial drugs, the decision of which drug to recommend becomes both critical and complex.

Drug efficacy assessment methodology appropriate to the situation existing in sub-Saharan Africa has been developed over the last 20 to 25 years. The goals of these studies are to assess antimalarials currently being used for the treatment of uncomplicated malaria. These data are critical for guiding the development of rational antimalarial drug policies and treatment guidelines. The duration of the resolution of symptoms, the proportion of patients experiencing a “clinical failure” within a pre-determined follow-up period, and the ability of anemic patients to improve their hematologic status have become the primary indicators of antimalarial drug efficacy [3].

This document presents a standardized protocol for assessing the therapeutic efficacy of antimalarial drugs in Africa utilizing the most current concepts of not only what data are needed to accurately judge antimalarial efficacy, but also what information is required by national decision makers to devise rational policies and guidelines for their countries. This protocol is based on experiences gained in drug efficacy testing in numerous countries throughout the world and follows a standardized WHO protocol for drug efficacy testing [4, 5].

Malaria in Ethiopia is highly unstable, with potential for epidemics. In Ethiopia, malaria transmission is largely determined by climate and altitude. Most of the transmission occurs between September and December, after the main rainy season from June to August. Certain areas, largely in the eastern part of the country including parts of Oromia, experience a second minor transmission period from April to May, following a short rainy season from February to March. Five main malaria eco-epidemiological strata are recognized:

- Stable, year round, transmission in the western lowlands and river basin areas of Gambella;
- Seasonal transmission in lowland areas <1,500 meters above sea level (m);
- Epidemic-prone areas in highland fringes between 1,500 – 2,500 m;
- Arid areas where malaria is only found near semi-permanent water bodies; and
- Malaria-free highland areas >2,500 meters.

Malaria is the leading communicable disease in Ethiopia. Overall, malaria accounts for up to 17% of outpatient consultations, 15% of admissions, and 29% of in-patient deaths (Federal Ministry of Health data, 2005/6). About 75% of the country is malarious (defined as *areas <2000 m*), with about 68% (i.e. 52 million) of the country’s total population living in areas at risk of malaria. Approximately 9.5 million clinical cases of malaria were reported annually between 2001– 2005 (range: 8.4 – 11.5 million), with an annual average of 487,984 laboratory confirmed cases over the same period (range: 392,419 – 591,442) (Federal Ministry of Health data, 2005/6). Approximately 70,000 people die of malaria each year in Ethiopia (Federal Ministry of Health data, 2005/6). Similarly, in Oromia Regional State malaria is considered to be the most important communicable disease. Three quarters of the region, i.e. 262 of 297 (88%) districts and 4,237 of 6,765 (63%) communities, are considered malarious, accounting for over 17 million persons at risk of infection. There are an estimated 1.5 to 2 million clinical cases per year, with malaria accounting for 20-35% of outpatient consultations, 16% of hospital admissions, and 18-30% of hospital deaths in the region.

*P. falciparum* (Pf)and *P. vivax* (Pv) are the two dominant parasite species with relative frequencies of 60% and 40%, respectively, although this proportion varies in geography and time with published ranges of 41-89% for Pf and 11-55% for Pv [6, 7]. Chloroquine (CQ) resistant Pf was first reported from Africa in 1978 [8] and became a major public health threat to Ethiopia in the 1990s. An evaluation conducted in Ethiopia from 1989–1991 noted overall 3.7% of those treated with chloroquine for falciparum malaria returned to the clinic within 2 weeks due to not being cured but 87.2% of those who returned demonstrated chloroquine resistance [9]. Reports of unsuccessful treatment of *P. falciparum* with chloroquine increased with time. By the late 1990s, 86-88% treatment failure of Pf to chloroquine were being reported which prompted the change of first-line treatment of Pf to sulphadoxine-pyrimethamine (SP) in 1998 [10, 11]. Studies evaluating Pf resistance to SP in 2001–2002 showed 2.6-32.0% treatment failure throughout Ethiopia [12-14]. Only a year later in 2003, a nation-wide study involving 11 sentinel sites showed 35.9% and 71.7% treatment failure with 14-day and 28-day follow-up, respectively. Falciparum malaria treatment failure of AL was noted to be 0.9% at baseline prior to its introduction in Ethiopia in 2004 [15]. Recent AL efficacy study for Pf by Aklilu Lemma Institute of Pathobiology in Alaba Health Center, Southern Nations, Nationalities, and People's Region (SNNPR), shows 0% resistance (paper in press). PCR corrected cure rates from other African countries has been also shown to be high (93.9–99%) [16-19].

Chloroquine is the first-line treatment for Pv malaria in Ethiopia, but with the spread of CQ-resistant Pf, Ethiopia recommends AL for the treatment of confirmed Pf and all cases of clinical malaria where diagnostics to determine the specific malaria species are not available. In areas co-endemic for Pf and Pv malaria, such as in Ethiopia, the adoption of AL as first-line Pf treatment raises the inevitability of a significant proportion of Pv malaria being treated with AL. Therefore, World Health Organization (WHO) recommends AL for the treatment of Pv, where AL has been adopted as first-line treatment for Pf. They also state that Pv response to ACT treatment is as good as or better than in falciparum malaria [20]. A study in Thailand demonstrated that the combination of AL and primaquine was as effective and well tolerated compared to chloroquine and primaquine for the treatment of Pv [21], whereas, an earlier study comparing CQ to artemether alone demonstrated no early treatment failures in either arm [22]. This proposed study would provide information on the response to AL treatment for Pv in Ethiopia where falciparum and vivax malaria coexist. Chloroquine resistant Pvhas remained rare in Africa with published resistance level of 2-4.6% in Ethiopia [11, 23]. In the recent past we have seen rapid development of resistance to newly introduced anti-malarial therapies, for this reason, it is critical to continuously monitor drug efficacy, to allow sufficient time to change national policy when drug efficacy begins to decline.

*P. vivax* unlike *P. falciparum* has a dormant stage [hypnozoites] that can persist in the liver and cause relapses by invading the bloodstream weeks, or even years later. Both CQ and AL treat only the blood stage parasites and have no impact on the liver stage infection. Primaquine can be used to eliminate hypnozoite forms (radical cure) after the acute infection (clinical cure) has been treated with either CQ or AL. This is often done in malaria-free areas such as the United States. However, it is not routinely done in malaria endemic areas. The national treatment guidelines in Ethiopia state that ”in malarious areas where there is a high risk of reinfection, and where the main purpose of treatment should be to bring about clinical cure rather than radical cure, administration of primaquine is not recommended [24].” In complying with national guidelines, our study will not administer primaquine to attempt radical cure but seek to evaluate the efficacy of CQ and AL in the immediate infection only.

# OBJECTIVES

To assess the therapeutic efficacy of AL for uncomplicated *P. falciparum* and *P. vivax* infections and chloroquine for *P. vivax* infection based on parasitologic, clinical, and hematologic parameters, we will conduct an open-label one-arm in-vivo efficacy assessment for *P. falciparum* and two-arm for *P. vivax*.

**Specific Objectives**

1. To measure the clinical and parasitological efficacy of current first-line therapies of AL for uncomplicated *P. falciparum*, by determining the proportion of patients with Early Treatment Failures (ETF), Late Clinical Failures (LCF), Late Parasitological Failures (LPF), or with Adequate Clinical and Parasitological Response (ACPR) during a 42-day follow-up period for *P. falciparum*, (See Annex I for WHO definitions of treatment outcomes for falciparum malaria)
2. To measure the treatment failure of AL and CQ for *P. vivax* infection during a 42-day follow-up period. (See Annex II for WHO definitions of *P. vivax* treatment failures)
3. To differentiate treatment failures with molecular testing and drug levels

# STUDY DESIGN

### Study Sites

Three potential evaluation sites near to Adama town in Oromia Regional State were selected based on availability of adequate numbers of cases of symptomatic, uncomplicated *P. falciparum* and *P. vivax* malaria infections, willingness of the selected health care facility staff to participate in the study and to support the work with laboratory space, and its proximity to Adama Reference Laboratory (Malaria Training Center). Adama, better knownas Nazreth, is a [city](http://en.wikipedia.org/wiki/City) in central [Ethiopia](http://en.wikipedia.org/wiki/Ethiopia) and is located in the [East Shewa Zone](http://en.wikipedia.org/wiki/Misraq_Shewa_Zone) of Oromia, at an elevation of 1712 meters, approximately 100 [km](http://en.wikipedia.org/wiki/Kilometre) southeast of [Addis Ababa](http://en.wikipedia.org/wiki/Addis_Ababa). Based on figures from the [Central Statistical Agency](http://en.wikipedia.org/wiki/Central_Statistical_Agency_(Ethiopia)) in 2005, this city has an estimated total population of 228,623.

The three potential health care facilities selected are:

1. Adama Malaria Training Center located in Adama town
2. Awash Melkasa Health Center (HC) located in Awash Melkasa town about 10 km from Adama town
3. Debrezeit Malaria Laboratory located approximately 50 km northwest of Adama Town.

Data from the three health care facilities collected in the past two months show a range of 7-42 cases of microscopy confirmed Pf and 14-399 cases of microscopy confirmed Pv. We would expect the number of malaria cases and especially Pf cases to increase during the high transmission season (October-December).

| Site | Oct-Dec 2006 | | Oct-Dec 2007 | | July-Aug 2008 | |
| --- | --- | --- | --- | --- | --- | --- |
|  | Pf | Pv | Pf | Pv | Pf | Pv |
| Adama Malaria Training Center |  |  | 37 | 158 | 20 | 91 |
| Awash Melkassa Health Center | 171 | 163 |  |  | 42 | 14 |
| Debrezeit Malaria Center | 941 | 1727 |  |  | 7 | 399 |

However, in Oromia state as well as all of Ethiopia, malaria incidence has been decreasing rapidly due to scale-up of preventive measures e.g. mass distribution of long-lasting insecticidal nets and indoor residual spraying. We will be tracking the number of malaria cases presenting to the sites in the weeks leading up to the study initiation. If the numbers are inadequate at the three suggested sites, we will consider adding or switching sites to ensure enrollment of sufficient cases in a timely manner. All potential health centers are under the jurisdiction of the Oromia Regional Health Bureau and the Ministry of Health. If the numbers are inadequate at the 3 selected sites and 1 alternate site previously named, we will select additional health care centers operated by the Oromia Regional Health Bureau in Oromia State to participate in this study based on the same criteria: location in Oromia Regional State, availability of adequate number of cases of symptomatic, uncomplicated *P. falciparum* and *P. vivax* malaria infections, willingness of the selected health care facility staff to participate in the study and to support the work with laboratory space, and proximity to Adama Reference Laboratory.

### Drugs

**Known efficacy and adverse effects of treatment drugs**

**● Artemether - lumefantrine (Coartem or AL):** Artemether-lumefantrine is a WHO prequalified anti-malarial; WHO certifies the quality, safety and efficacy of the medication, and verifies that the manufacturer complies with WHO Good Manufacturing Practices. AL is currently the first line anti-malarial recommended by Ethiopian Ministry of Health for the treatment of uncomplicated falciparum infection and treatment of clinical malaria cases without laboratory confirmation which comprises of non-malaria cases, falciparum cases, and vivax cases. Adverse events are generally mild, most commonly GI (vomiting and diarrhea) and hematologic (anemia and eosinophilia) [16]. Its safety was demonstrated in studies from Ethiopia and Uganda [15, 25].

- **Chloroquine (CQ):** Chloroquine, a 4-aminoquinoline, was recognized as an effective and safe antimalarial in 1946, and was the most widely used drug against malaria until significant resistance to chloroquine rendered it ineffective against Pf. CQ is currently recommended by Ethiopian Ministry of Health for the treatment of vivax infection. Side effects include dizziness, skeletal muscle weakness, mild gastrointestinal disturbances (nausea, vomiting, abdominal discomfort, and diarrhea), and pruritus [26].

**Pharmacokinetics**

- **Artemether - Lumefantrine (Coartem):** artemether has a short t ½~ 1.5 hours, while lumefantrine has a long elimination half-life, 4 to 6 days
- **Chloroquine:** chloroquine has a long elimination half-life of 1-2 months.

**Drug Dosing and Regimens: All patients will be weighed to determine the accurate weight-based dose for both drugs.**

- **Artemether-lumefantrine** (Coartem; Novartis) administered twice daily for three days as tablets containing 20 mg of artemether plus 120 mg of lumefantrine in a fixed dose combination at a dosage [24].

| Weight (kg) | Age | Day 1 | | Day 2 | | Day 3 | |
| --- | --- | --- | --- | --- | --- | --- | --- |
| Morning | Evening | Morning | Evening | Morning | Evening |
| 5–14 | 3mo–2yrs | 1 | 1 | 1 | 1 | 1 | 1 |
| 15–24 | 3–7 yrs | 2 | 2 | 2 | 2 | 2 | 2 |
| 25–34 | 8–10 yrs | 3 | 3 | 3 | 3 | 3 | 3 |
| > 35 | 10+ yrs | 4 | 4 | 4 | 4 | 4 | 4 |

- **Chloroquine:** Total of 25mg base per kg over 3 days (10 mg base/kg on Days 1 and 2, and 5 mg base/kg on Day 3) [24]. 500 mg tablets and 10mg/ml syrup formulations. We will use the syrup formulation for children < 4 years of age.

| Weight (kg) | Age | Day 1 | Day 2 | Day 3 |
| --- | --- | --- | --- | --- |
| 5–6 | <4 mo | ¼ tablet  (5 ml syrup) | ⅛ tablet  (5 ml syrup) | ⅛ tablet  (2.5 ml syrup) |
| 7–10 | 4–11 mo | ¼ tablet  (7.5 ml syrup) | ¼ tablet  (7.5 ml syrup) | ¼tablet  (5 ml syrup) |
| 11–14 | 1–2 yrs | ½ tablet  (12.5 ml syrup) | ½ tablet  (12.5 ml syrup) | ¼ tablet  (7.5 ml syrup) |
| 15–18 | 3–4 yrs | ½ tablet  (15 ml syrup) | ½ tablet  (15 ml syrup) | ½ tablet  (15 ml syrup) |
| 19–24 | 5–7 yrs | ¾ tablet  (20 ml syrup) | ¾ tablet  (20 ml syrup) | ½ tablet  (15 ml syrup) |
| 25–35 | 8–10 yrs | 1¼ tablet | 1¼ tablet | ½ tablet |
| 36–50 | 11–13 yrs | 1½ tablet | 1½ tablet | 1 tablet |
| > 50 | 14+ yrs | 2 tablet | 2 tablet | 1 tablet |

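### The chloroquine table's 15–18 kg row gives the same dose on all three days, which contradicts the stated 10/10/5 mg base/kg split

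*Protocol*

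**What the plan says.** The Drug Dosing and Regimens section gives chloroquine in two forms, a rule and a weight-band table. The rule is "Total of 25mg base per kg over 3 days (10 mg base/kg on Days 1 and 2, and 5 mg base/kg on Day 3". The table row at issue reads "15–18 | 3–4 yrs | ½ tablet (15 ml syrup) | ½ tablet (15 ml syrup) | ½ tablet (15 ml syrup".

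The products are described as "500 mg tablets and 10mg/ml syrup formulations", with no statement of whether 500 mg is salt or base. On who gets which, the section says: "We will use the syrup formulation for children < 4 years of age". Because the row is labelled 3–4 years, both its columns are in use: syrup for three-year-olds and tablets for four-year-olds. The protocol does not say whether rule or table prevails when they differ.

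**The concern.** The rule fixes the Day 3 dose at half the Day 1 dose. A row with three equal doses cannot satisfy it at any product strength or body weight. Children in this band are eligible (above 6 months, at least 5 kg), so the conflict affects what real participants receive. For a 16 kg child the rule gives 5 × 16 = 80 mg on Day 3, while the syrup column gives 15 × 10 = 150 mg. The re-dosing instruction after vomiting, a full or half repeat dose, inherits the same ambiguity.

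The study's purpose is to estimate the efficacy of a named regimen. The regimen should therefore have one reading, and the delivered mg base/kg should be calculable from the protocol. For tablets it is not.

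**Working it through.** **Inputs**, all from Drug Dosing and Regimens: the 10/10/5 rule; the chloroquine table; syrup 10 mg/ml. Two assumptions are needed for mg/kg figures but not for ratios: the syrup strength is in mg base, and a tablet holds 250–300 mg base. The second comes from the table's own tablet/syrup pairs at 11–24 kg:

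- ½ tablet = 12.5 ml: 125 / 0.5 = 250 mg
- ¾ tablet = 20 ml: 200 / 0.75 = 267 mg
- ½ tablet = 15 ml: 150 / 0.5 = 300 mg

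**Step 1. The rule.** 10 + 10 + 5 = 25 mg/kg, and Day 3 / Day 1 = 5/10 = 0.50. The 11–14 kg tablet cells (½/½/¼) reproduce this: 0.25/0.50 = 0.50. So do the cells above 50 kg (2/2/1).

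**Step 2. The 15–18 kg row.** Tablets: 0.5/0.5 = 1.00. Syrup: 15/15 = 1.00. Neither depends on strength.

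**Step 3. Delivered dose**, as dose / 18 to dose / 15:

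| Product | mg per day | Each day, mg/kg | Total, mg/kg |
| --- | --- | --- | --- |
| Syrup, 10 mg base/ml | 150 | 8.3–10.0 | 450 mg: 25.0–30.0 |
| Tablet, 300 mg base | 150 | 8.3–10.0 | 450 mg: 25.0–30.0 |
| Tablet, 250 mg base | 125 | 6.9–8.3 | 375 mg: 20.8–25.0 |

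For syrup, Day 3 relative to the stated 5 mg/kg is 8.3/5 = 1.7 to 10.0/5 = 2.0.

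**Step 4. Is it rounding?** The Day 3 target is 5 × 15 = 75 mg to 5 × 18 = 90 mg. At 300 mg base, ¼ tablet is 75 mg and ½ is 150 mg, with midpoint 112.5 mg. At 250 mg base they are 62.5 and 125 mg, with midpoint 93.75 mg. The whole target range lies below both midpoints, so ¼ tablet is the nearest quarter at every weight in the band. In syrup the target is 7.5–9 ml, and 7.5 ml is already used on Day 3 in the 11–14 kg row. Rounding does not produce 15 ml or ½ tablet.

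**Step 5. Other rows.** In the 19–24 kg row (¾/¾/½, ratio 0.67) the Day 3 target is 5 × 19 = 95 mg to 5 × 24 = 120 mg. At 250 mg base this lies above the 93.75 mg midpoint, so ½ tablet is the nearest quarter throughout. The syrup cells in that row (20/20/15 ml) sit beside an age label of 5–7 years, where syrup would not normally be used. The 25–35 kg row (0.5/1.25 = 0.40) and the 36–50 kg row (1/1.5 = 0.67) also depart from 0.50. At 250 mg base their Day 3 doses are 125 mg and 250 mg, which equal 5 mg/kg at 25 kg and 50 kg, both inside their bands.

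**Step 6. What a correction does to the total** (syrup, 10 mg base/ml):

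- 15/15/10 ml: 400 mg, 400/18 = 22.2 to 400/15 = 26.7 mg/kg, and below 25 for every child above 400/25 = 16 kg.
- 17.5/17.5/10 ml: Days 1 and 2 are 175/18 = 9.7 to 175/15 = 11.7 mg/kg; Day 3 is 100/18 = 5.6 to 100/15 = 6.7 mg/kg; the total is 450 mg, 25.0–30.0 mg/kg. Day 3 / Day 1 = 10/17.5 = 0.57.

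**The case against.** The strongest reply is that the rule also sets a total of 25 mg base/kg, and the flat row serves that total better than a literal halving of Day 3. With Days 1 and 2 as printed, ¼ tablet on Day 3 gives 375 mg at 300 mg base (20.8–25.0 mg/kg) or 312.5 mg at 250 mg base (312.5/18 = 17.4 to 312.5/15 = 20.8 mg/kg). For a drug whose elimination half-life the protocol puts at 1–2 months, the total plausibly matters more than the daily split. The row may also come from the cited national guideline, which is not available here.

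Part of this stands: the total must be protected in any correction, and the row may be deliberate. It does not remove the conflict. The protocol prints both the split and the row, explains neither departure nor precedence, and nobody can follow both.

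A reader might go further and call the whole table wrong, pointing to the 19–24, 25–35 and 36–50 kg rows. The documents do not support that. Those rows are compatible with coarse tablet rounding at some strengths, whereas the 15–18 kg row is not. A reader might also take the 500 mg tablet as 500 mg base and infer a total of 750/18 = 41.7 to 750/15 = 50.0 mg/kg. The table's own syrup equivalents, implying 250–300 mg, argue against it.

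**Conclusion.** The point holds for one row. At 15–18 kg the table and the stated split contradict each other in both formulations, independently of strength. With syrup at 10 mg base/ml, Day 3 is 1.7–2.0 times the stated dose and the total is 25.0–30.0 mg/kg. With tablets the total runs from 20.8 to 30.0 mg/kg over 250–300 mg base, and the protocol does not say where in that range it falls.

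It would be wrong to infer that these children are underdosed on syrup, or that the chloroquine failure rate is materially biased. The effect is probably small. It cannot be quantified, because the share of the arm weighing 15–18 kg is not given. No endpoint, sample size or analysis changes. It is nonetheless worth correcting, because it determines the study drug dose given to eligible children.

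**What to change.** State the tablet and syrup strengths in mg base, check the table against the cited national guideline, and then do one of the following.

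1. If the table is the intended regimen, say that it governs, and restate the rule as a total of about 25 mg base/kg over three days.
2. If the split is intended, correct the 15–18 kg row so that Day 3 is about half of Day 1 and the total stays near 25 mg/kg. Syrup 17.5/17.5/10 ml is one example. Pharmacy should set the matching tablet fractions once the base content is known.

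Do not reduce Day 3 alone: 10 ml with Days 1 and 2 unchanged leaves an 18 kg child at 22.2 mg/kg.

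As a minor tidy-up, the last artemether-lumefantrine row, "> 35 | 10+ yrs | 4 | 4 | 4 | 4 | 4 | 4", follows a band ending at 34 kg and so leaves out exactly 35 kg. The intended reading is obvious; change the sign to ≥ 35.

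The cost is one restated sentence or one corrected row, a line on strengths and one boundary sign, made before dispensing sheets are issued. No new data or visits are needed.
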